### Study population and selection criteria

The study will comprise three groups: an intervention arm (group A) and two control arms (groups B and C) (see Fig. 1). The targets of groups A and B will be children living with HIV and their caregivers. Randomization will be performed for groups A and B using a 1:1 allocation protocol. The targets of group C will be HIV-uninfected children and their caregivers, comprising children age-matched with those in group A. Children eligible for groups A and B of the trial must meet all of the following inclusion criteria at randomization: (1) age 3–15 years, (2) have a patient ID at the National Pediatric Hospital, and (3) have received ART for at least 3 months. Children eligible for group C must be aged 3–15 years and must not have been diagnosed with HIV infection. For caregivers in all groups, individuals will be eligible if they are aged ≥ 18 years and self-report as the primary caregiver of the respective child.

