### Sample size

We calculated the sample size for the intervention and control groups as follows. We estimated that the intervention may suppress the increment of DMFT for around 17% based on the results of a previous study conducted in Cambodia among 8000 uninfected school children in five provinces. In that study, increments of DMFT of intervention and control groups were 0.82 and 0.99, respectively, after a 2-year intervention [35]. According to our situation analysis survey, which was conducted at the same study site in February 2017, for children living with HIV aged 8–15, the mean DMFT was 4.34 (standard deviation 3.3). We estimate that the intervention may suppress the increment of DMFT by 0.7 point, which equates to the 17% decrease in the mean DMFT. To detect this difference in our intervention group, at a power of 80% and a 5% significance level, 260 samples will be required for each group with a potential attrition of approximately 10%. In total, 780 pairs will be required for the three groups.

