### Statistical analyses

Baseline and endline surveys will be conducted to assess changes in each outcome in both the intervention and control groups. To minimize overestimation of intervention impact, all intervention outcomes will be estimated with an intention-to-treat analysis. Initially, survey data will be stratified by different age groups: 3–5 years old, 6–11 years old, and 12–15 years old. Then, the data will be descriptively analyzed to assess the distributions of various factors related to the children and caregivers under the study. Next, bivariate analyses will be conducted to assess the correlations of each oral health indicator (DMFT, debris index, bacterial number, salivary pH, salivary flow, oral-health related quality of life) with different variables, using the chi-square test (or Fisher’s exact test when a count is smaller than five) for categorical variables, and Student’s *t* test for continuous variables. Then, we will apply a generalized estimating equation model [41] adjusted for basic demographic characteristics (e.g., sex) and factors identified as significantly associated with the outcome in the bivariate analyses. The statistical significance will be set at a *p* value < 0.05. All data analyses will be performed using IBM SPSS, version 24.0 (SPSS Inc., Chicago, IL, USA).

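### On the protocol's own inputs (difference 0.7, SD 3.3), 260 children per arm with 10% attrition gives about 63% power for the randomized comparison, not the stated 80%

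*Protocol article*

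**What the plan says.** All the inputs stand in the Sample size section of the protocol article.

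- Effect: "We estimate that the intervention may suppress the increment of DMFT by 0.7 point, which equates to the 17% decrease in the mean DMFT".
- Variability, from a survey at the study site in children with HIV aged 8–15: "the mean DMFT was 4.34 (standard deviation 3.3". No other SD appears in the section.
- Error rates and result: "at a power of 80% and a 5% significance level, 260 samples will be required for each group with a potential attrition of approximately 10" per cent.

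The Study population and selection criteria section fixes the allocation of the two HIV-infected groups: "Randomization will be performed for groups A and B using a 1:1 allocation protocol". The Statistical analyses section sets significance at p < 0.05 and does not mention a one-sided test.

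**The concern.** The section prints a complete set of inputs and an answer, so a reader can check one against the other. With an SD of 3.3, a difference of 0.7 is about 0.21 of an SD (0.7/3.3 = 0.212). That is a small standardized effect, and about 234 evaluable children per arm looks too few to detect it with 80% power.

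DMFT change is the primary outcome, and this calculation is the stated justification for randomizing 520 children. If the power claim is wrong, the chance of missing the targeted effect is larger than the protocol tells its readers. A non-significant result could then be taken as stronger evidence against a 0.7-point effect than the design supports.

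**Working it through.** **Inputs.** Difference d = 0.7, SD = 3.3, power 80%, significance level 5% and attrition 10% (Sample size); allocation 1:1 (Study population and selection criteria). Sidedness is not stated, so two-sided is taken first. 260 enrolled × 0.9 = 234 evaluable per arm.

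**Trying to reproduce 260.** Normal approximation for two means:

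n per arm = 2 (z₀.₉₇₅ + z₀.₈₀)² SD² / d² = 2 × (1.960 + 0.842)² × 3.3² / 0.7² = 348.9, so 349 evaluable.

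With attrition: 349 / 0.9 = 387.8, so 388 enrolled per arm. The t-based version gives 350 evaluable. The stated 260 is not reproduced.

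**Power of the planned design.**

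- 234 evaluable per arm: standard error = 3.3 × √(2/234) = 0.305; 0.7/0.305 = 2.294; power = Φ(2.294 − 1.960) = 63.1% (62.9% t-based).
- All 260 evaluable, no attrition: power = 67.7%.
- Difference detectable with 80% power at 234 per arm: 2.802 × 0.305 = 0.855.

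**Other readings, 1:1 allocation, SD 3.3.**

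| Difference | Test | Evaluable per arm | Enrolled per arm at 10% attrition | Power at 234 per arm |
|---|---|---|---|---|
| 0.7 | two-sided | 349 | 388 | 63% |
| 0.7 | one-sided 5% | 275 | 306 | 74% |
| 17% × 4.34 = 0.7378 | two-sided | 315 | 350 | 68% |
| 0.7378 | one-sided 5% | 248 | 276 | 78% |

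None gives 260 enrolled with the stated attrition. The last row would fit within 260 only if nobody were lost, and it needs both a one-sided test and a difference other than the one stated.

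**Pooling the two control groups.** Comparing A with B and C combined (1:2) changes the factor 2 in the formula to 1.5.

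- d = 0.7: 1.5 × 2.802² × 3.3² / 0.7² = 261.7, so 262 in group A before attrition and 262/0.9 = 291.1, so 292, after it.
- d = 0.7378: 235.5, so 236, and 236/0.9 = 262.2, so 263 enrolled (260 if the inflation is done as n × 1.1).

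The second is the only near match to 260 once attrition is included.

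**What would make 234 per arm sufficient for 0.7.** The effective SD would have to be at most 0.7 / (2.802 × √(2/234)) = 2.70. The variance ratio is (2.70/3.3)² = 0.671. Assuming an SD of 3.3 at both visits and a baseline-endline correlation ρ:

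- baseline-adjusted analysis: 1 − ρ² = 0.671, so ρ = 0.574;
- change score: 2(1 − ρ) = 0.671, so ρ = 0.665.

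**The case against.** The strongest reply is that 3.3 is the wrong SD for this outcome. It describes DMFT at one time in children aged 8–15, whereas the primary outcome is change over two years. If baseline and endline DMFT are well correlated, true power is higher. Taking ρ = 0.6 as an assumption, 234 per arm gives 82% power with baseline adjustment and 73% with a change score; at ρ = 0.7 it gives 89% and 84%. This stands as a limit on the conclusion: 63% is what the protocol's inputs imply, and it is not an estimate of the trial's true power. It does not rescue the stated calculation. The section gives no SD for the increment and no correlation, and the generalized estimating equation model in Statistical analyses is not said to adjust for baseline DMFT. The argument also cuts both ways: at ρ = 0.5 the SD of the change score is again 3.3, and below 0.5 it is larger.

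A second reply is that a full protocol might hold the missing correlation. That is possible, but the article prints 3.3 as the SD beside the 80% claim, and the two do not agree.

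A third is that pooling groups B and C comes close to 260. The match needs 0.738 in place of the stated 0.7, the section does not describe pooling, and group C is neither randomized nor HIV-infected. It cannot support a power claim for the randomized comparison of A with B.

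Two further cautions stand. The SD comes from ages 8–15, while the Recruitment section takes 20 children per year of age from 3 to 15, so 100 of each 260 (ages 3–7) lie outside the range that supplied it. Also, the 17% in the cited school study is a reduction in the increment (0.99 to 0.82, a difference of 0.17), but the section applies it to the mean level of 4.34 to reach 0.7. That is a separate weakness of the effect size, and correcting the power statement does not remove it.

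**Conclusion.** The concern holds. For the 1:1 randomized comparison, two-sided at 5%, a difference of 0.7 with SD 3.3 requires 349 evaluable (388 enrolled) children per arm. The planned 260 enrolled gives 63% power, so the risk of missing the targeted effect is about 37% rather than 20%. The detectable difference at 80% power is about 0.85.

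These figures rest on the stated SD applying to the quantity compared. What is established is that the 260 and the 80% do not follow from the printed inputs. Whether the trial is underpowered in fact depends on a baseline-endline correlation that the protocol does not give.

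**What to change.** Keep 260 per arm and correct the Sample size section in one of two ways.

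1. State what follows from the inputs: 234 evaluable per arm gives 63% power for a difference of 0.7, and 80% power for about 0.85, at SD 3.3 and two-sided 5%.
2. Base the calculation on endline DMFT adjusted for baseline DMFT. State the assumed correlation and where it comes from, rather than choosing it to yield 80%, and name that adjusted comparison of A with B as the primary analysis in Statistical analyses. At SD 3.3, 80% power for 0.7 needs a correlation of at least 0.574 (0.57 falls just short, at 79.7%).

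In either case, state the sidedness of the test and say that the calculation refers to A versus B.

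The cost is wording: a less favourable power figure, or one more stated and justified assumption. Baseline DMFT is already collected and no extra children are needed. Enrolling 388 per arm (776 in total) would also meet the 80% claim at SD 3.3, and the Recruitment section lists 1113 eligible children, but that is a much larger change than the correction needs.

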### Recruitment

Recruitment will be conducted via a multiple-step process. First, children living with HIV aged 3–15 years will be identified from the patient lists of the National Pediatric Hospital. According to the list, 1113 children are eligible based on the study criteria. Twenty children in each age category from 3 to 15 years old will be randomly selected from each list to yield 260 children each for groups A and B. Second, the same patient lists will be used to identify one district wherein the largest number of children living with HIV reside. The children in group C will be selected from that district, using lists of residents aged 3–15 years that have been compiled by a local non-governmental organization, in collaboration with the local authorities. Twenty children per age category from 3 to 15 years will be randomly selected from those lists to yield 260 children for group C. The children deemed eligible for the intervention will be provided with information about the study, and the research assistants will seek an expression of interest from the caregivers and the children. They will be contacted by the research assistants to arrange a suitable time for the baseline survey. Prior to the survey, the research assistants will obtain their written informed consent.

### Randomization

After the baseline survey, the children living with HIV will be randomly allocated to an intervention group in a 1:1 ratio. A computerized algorithm will be used to generate a randomization scheme to assign participants to the study arms. The allocation will be implemented by a data analyst who is not a primary member of the study team. A member of the research team will inform the participants of their allocation. The research assistants, principal investigator, and primary study team members will be blinded to the group allocations until after the participants have completed the baseline assessment.

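### The stated allocation does not secure the quota of 20 children per year of age in each HIV arm, and the role of the age bands in the primary test is left open

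*Protocol article*

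**What the plan says.** All references are to the protocol article.

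- **Recruitment.** For the children with HIV, 20 at each age from 3 to 15 "will be randomly selected from each list to yield 260 children each for groups A and B". For the uninfected children: "Twenty children per age category from 3 to 15 years will be randomly selected from those lists to yield 260 children for group C".
- **Study population and selection criteria.** Group C is described as "comprising children age-matched with those in group A". The equal quota in Recruitment is the only matching mechanism given.
- **Randomization.** "After the baseline survey, the children living with HIV will be randomly allocated to an intervention group in a 1:1 ratio". On method: "A computerized algorithm will be used to generate a randomization scheme to assign participants to the study arms". No stratum, block or other balancing by age is named.
- **Statistical analyses.** "Initially, survey data will be stratified by different age groups: 3–5 years old, 6–11 years old, and 12–15 years old". Description, bivariate tests and a generalized estimating equation (GEE) model follow in that order. Sex is the only demographic covariate named, and it is given as an example. Other covariates enter if they are significant in the bivariate step. The section does not say whether the model is fitted in each band or once over all ages.
- **Sample size.** There is one calculation for the whole group: a difference of 0.7 DMFT, SD 3.3 from a survey of children aged 8–15, 80% power, 5% significance, 260 per group including about 10% attrition.

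**The concern.** There are two separate problems.

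**How the arms are formed.** The quota speaks as if each HIV arm holds 20 children at every age, but the arms do not exist until after the baseline survey. If 20 per age were drawn for A and another 20 for B, the draw itself would be the allocation, which conflicts with the Randomization section. If 40 per age are drawn and then randomised, each arm holds 20 per age only when allocation is balanced within age, and the article names nothing that does this. Group C is fixed at 20 per age by its own draw, so its year-by-year match to A depends on the same missing step. A versus C is part of the stated objectives and is not protected by randomisation, so age matters most there.

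**What the age bands are for.** Banding comes first, ahead of every test, and no pooled primary test is stated. A reader could carry out three separate band analyses and still be following the text. The sample size was not set for that: each band would have low power, and the false-positive rate over the three would exceed 5%.

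**Working it through.** **1. The quota.** Ages 3 to 15 are 13 years of age.
- 13 × 20 = 260, one arm.
- 520 / 13 = 40 children with HIV per year of age over A and B together.

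The totals in Recruitment are therefore consistent. The open question is how 40 become 20 and 20.

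**2. Age balance if allocation ignored age (an assumption, since the article does not say).** Split 520 children, 40 per year of age, at random into two arms of 260.
- SD of the number in A at one age = √[260 × (40/520) × (480/520) × (260/519)] = √9.25 = 3.04. The 95% range is 14 to 26.
- The chance of exactly 20 at a given age is 13%. Exactly 20 at all 13 ages occurred in 0 of 100,000 simulated allocations.
- Simulated 95% ranges for band size in A: 51–69 (planned 60), 109–131 (planned 120), 70–90 (planned 80).
- In 95% of allocations the difference in mean age was at most 0.64 years for A–B and at most 0.32 years for A–C, with C at its quota mean of 9.0 years.

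So the exact counts would be lost, but average age would stay close.

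**3. The plan's own sample size.** Per arm, two-sided 5%, 80% power: n = 2 × (1.960 + 0.842)² × 3.3² / 0.7² = 349 evaluable, and 349 / 0.9 = 388 recruited. The stated 260 is not reproduced. A one-sided test gives 275 evaluable and 306 recruited. With 260 × 0.9 = 234 evaluable per arm, pooled two-sided power is 63%. An SD of about 2.70 would bring it to 80%. That is a separate issue, noted here because it is the baseline for the next step.

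**4. Power if the effect were tested within bands.** The bands cover 3, 6 and 4 years of age, so 60, 120 and 80 per arm, or 54, 108 and 72 after 10% attrition. Power = Φ(0.7 / [3.3 × √(2/n)] − 1.96).

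| Band | Evaluable per arm | 0.7 / SE | Power, SD 3.3 | Power, SD 2.70 |
|---|---|---|---|---|
| 3–5 | 54 | 0.7/0.635 = 1.10 | 20% | 27% |
| 6–11 | 108 | 0.7/0.449 = 1.56 | 34% | 48% |
| 12–15 | 72 | 0.7/0.550 = 1.27 | 25% | 34% |

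Three independent tests at 5%: 1 − 0.95³ = 14.3% chance of at least one false positive.

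**5. Are the two problems linked?** Hardly. With band size in A at its 2.5th percentile under unstratified allocation, band power is 19%, 34% and 24%, almost the same as in the table. Low band power comes from splitting the sample. A single test combining the three bands with weights keeps the pooled 63%, because 54 + 108 + 72 = 234.

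**The case against.** The strongest reply is that the conflict is read into silence. The article mentions a computerised algorithm and does not say that it is simple or unstratified. Block and stratum details are often left to a full protocol. Drawing 40 per age and randomising within age would satisfy both Recruitment and Randomization. Group C is promised only as age-matched, and equal quotas give an approximate match. Sex is only an example covariate, so age is not excluded. Nor does the analysis section say that each band is tested for confirmation: the step directly after banding is descriptive, and elsewhere efficacy is described as intervention against control with no mention of bands.

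Much of this stands. A reader might infer that allocation is plainly unstratified, that the age match is therefore lost, and that the pooled power no longer applies. The documents support none of the three. The first is an inference from silence. On the second, only exact year-by-year counts are at risk, mean ages would stay close, and A–B remains a valid randomised comparison. The third holds only if the primary comparison is made separately by band, which the text leaves open. A reader might also infer that children change band during the study. By age at survey, six of the 13 entry ages (4, 5, 10, 11, 14, 15; 6 × 20 = 120 of 260 per arm) would change band or pass 15 by endline, but nothing says that bands are reassigned.

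What the reply does not remove is that the article commits to a per-age quota in each arm and a match that rests on it, then states an allocation that does not deliver them. It also places age banding before all testing while sizing only the pooled comparison.

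**Conclusion.** The point holds as two separate shortcomings in what the article fixes.

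First, the quota of 20 per year of age in each HIV arm, and with it the exact A–C age match, is not secured by the stated randomisation. The consequence is modest: an SD of about 3 children per year of age in A if allocation is unstratified, with small differences in mean age and no threat to the validity of A–B.

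Second, the role of the age bands in the primary test is undefined. If the bands are tested separately, power is about 20%, 34% and 25%, with a 14% chance of at least one false positive.

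The band figures assume a two-sided 5% level, the same 0.7 effect and SD 3.3 in every band, and 10% attrition in each. The SD comes from ages 8–15, so it is untested for the youngest band and for part of the middle one. The 14% assumes three independent tests without adjustment. This should be corrected: the change is small and removes both ambiguities.

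**What to change.** - **Recruitment and Randomization.** State that up to 40 children with HIV per year of age are drawn and, after baseline, randomised 1:1 in blocks within year of age, or within age band where a year has too few children.
- **Primary analysis.** Make one pooled A–B comparison of DMFT change primary, with age as a prespecified covariate or stratification factor rather than one that enters through bivariate significance. Include age in the A–C comparison as well.
- **Age bands.** Define them by age at randomisation. Report band effects as subgroup estimates with a treatment-by-age interaction.

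The cost is a little set-up work on the randomisation list and some rewording, with no added participants. Two limits should be stated. Exactly 20 per arm at each age needs enough consenting children at every age, and the article gives only a total of 1113 eligible children with no age breakdown. Stratified allocation does not by itself raise power within a band: 80% for 0.7 at SD 3.3 would need 349 evaluable per arm in each band.

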**Methods:**

A randomized controlled trial will be conducted in Phnom Penh from May 2018 to April 2020. Among 520 dyads of children living with their respective caregivers, half will be randomly allocated to the intervention group and the other half to the control group. Children aged 3–15 years who are currently receiving antiretroviral therapy at the National Pediatric Hospital will be recruited. In addition, 260 HIV-uninfected children (age-matched to the intervention group) will be recruited from the communities. They, together with their caregivers, will comprise the second control group. The main components of the intervention will include oral health education sessions for the children, as well as daily oral self-care under the supervision of their caregivers. The primary study outcome will be the change in oral health status including the number of decayed, missing, or filled permanent teeth, and the secondary outcome will be CD4 count. The effects of the intervention will be assessed by comparing outcome indicators between the children in the intervention and those in the control groups.

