### Interventions

Children and caregivers in group A will receive an intervention for 2 years (May 2018–April 2020). The main components of the intervention will comprise oral health education sessions and daily oral self-care. Prior to the intervention, two dental assistants from the National Pediatric Hospital will be appointed to receive a 1-day training course in conducting the oral health education sessions and intervention follow-up. Subsequently, these professionals will disseminate oral health education sessions to the children and caregivers under the supervision of the dentist every 4 months during the 2-year intervention period (in total six sessions for each participant). The initial education session will be provided with the contents presented in Table 1. The dental assistants will also provide the follow-up sessions to the initial session. Each 60-min session, including practice of the oral health procedure, will be attended by groups of 10 child-caregiver pairs. The education session will aim to teach the children and caregivers about correct brushing and the importance of daily oral care. Teaching tools will be developed based on publicly accessible basic oral health education materials which are used in Japan and the USA at school or dental clinics [33, 34].

**Table 1 Tab1:** Contents of oral health education session

Session 1: Knowledge	
1. What is tooth decay?	
2. Causes and prevention of tooth decay	
Session 2: Practice	
1. Brushing	
2. Flossing	
Session 3: Evaluation of oral health status	
1. Check plaque status using tester	
Session 4: Home-based daily oral care	
1. What one needs to do at home for daily care	
2. Follow-up schedule	

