The children and caregivers will practice home-based daily oral care. Each child will receive a toothbrush, two tubes of fluoride-containing toothpaste, and three packs of dental floss at every education session. During the session, the children will be advised to brush daily after breakfast, lunch, and dinner by themselves or with the help of a caregiver at home. To maximize the intervention adherence, the children will receive a daily record notebook to keep their daily oral care practice. In the notebook, a short oral care guide is presented to which the children and caregivers can refer any time at home. Also, the children affix a seal to the daily record notebook after each brushing and evaluate their weekly oral health practice on the checklist. The intervention will be discontinued at any time should the participant request it. Participants can receive any concomitant care and intervention during the trial.

The participants of groups B and C (randomized control arms) will not receive specific interventions for oral health management. Participants in all groups can receive any type of dental care as needed at a clinic, but they will be responsible for any expenditure.

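### Children are randomised one by one although caregivers are trained and care is given at home, and no stated rule keeps children of one caregiver in the same arm

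*Protocol article*

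**What the plan says.** **Sampling.** Recruitment in the protocol article works from hospital patient lists: "According to the list, 1113 children are eligible based on the study criteria". Then "Twenty children in each age category from 3 to 15 years old will be randomly selected from each list", giving 260 for each of groups A and B.

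**Allocation.** After the baseline survey, "the children living with HIV will be randomly allocated to an intervention group in a 1:1 ratio". The abstract words the unit differently: "Among 520 dyads of children living with their respective caregivers, half will be randomly allocated to the intervention group". The Sample size section also counts pairs.

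**Who receives the intervention.** Under Interventions, "Children and caregivers in group A will receive an intervention for 2 years", and the sessions teach both. "The children and caregivers will practice home-based daily oral care", with a short guide that both can consult there. The abstract adds that daily self-care takes place under caregiver supervision. The toothbrush, toothpaste and floss are handed to each child. Groups B and C get no specific oral health intervention.

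**Who may be a caregiver.** The selection criteria ask for an adult who will "self-report as the primary caregiver of the respective child". They set no number of children per caregiver.

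The Statistical analyses section and the limitations in the Discussion do not mention shared caregivers.

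**The concern.** Part of the intervention is a change in what the caregiver knows and does at home. A caregiver with two children on the hospital list can have both sampled, because children of different ages sit in different age cells and each cell is drawn separately. If the two are then allocated apart, one adult is trained for the child in group A and also looks after the child in group B. That adult cannot set the training aside, and the first child's supplies are in the same home.

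The group B child is then partly treated. Under the planned intention-to-treat comparison this shrinks the A versus B difference in DMFT, and in CD4 count if the intervention affects it. An analysis plan written later cannot undo a split allocation, so the matter has to be settled when children are sampled or randomised.

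**Working it through.** **1. Is splitting possible under the stated scheme?** There are 13 years of age (3 to 15), 20 children per year and two groups: 13 x 20 x 2 = 520, which matches the article. The child is the unit drawn and the unit allocated. Calling the unit a dyad changes nothing, since two children of one caregiver form two dyads that can go to different arms. Splitting is therefore possible.

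**2. Chance that a given pair is split.**
- Sampling fraction: 520/1113 = 0.467. This is an average. A fixed number is drawn per year of age, so the fraction differs between ages, and the age distribution of the list is not given.
- Both children sampled: 0.467² ≈ 0.218.
- Allocated apart, given both sampled: 260/519 = 0.501.
- Overall: 0.218 x 0.501 ≈ 0.109, or about 11% of listed pairs.

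**3. Expected number of split pairs.** The share f of listed children who have one other listed child under the same caregiver is not in the documents. It is assumed here, with all such children in pairs. Pairs on the list = 1113 x f/2. With full carry-over, the effect is 0.7 x (1 − share of B exposed), where 0.7 is the DMFT difference in the Sample size section.

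| Assumed f | Pairs on list | Both sampled | Split | Share of 260 in B | Effect, full carry-over |
|---|---|---|---|---|---|
| 5% | 27.8 | 6.1 | 3.0 | 1.2% | 0.692 |
| 10% | 55.7 | 12.1 | 6.1 | 2.3% | 0.684 |
| 20% | 111.3 | 24.3 | 12.2 | 4.7% | 0.667 |

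With half carry-over the effects are 0.696, 0.692 and 0.684.

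**4. Effect on power.** The stated 260 per group does not reproduce from the article's inputs. With a difference of 0.7, SD 3.3, two-sided 5% and 80% power, n = 2 x (1.96 + 0.842)² x 3.3²/0.7² ≈ 349 per arm, or 388 after dividing by 0.9 for attrition. That is a separate matter, but it sets the starting point. With 234 evaluable per arm (260 x 0.9), power is 63.1%. With full carry-over it falls to 62.1%, 61.1% or 59.0% for the three values of f, a loss of about 1 to 4 percentage points.

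**5. Cost of keeping a caregiver's children together.** Design effect = 1 + (m − 1) x ICC, where m is the size-weighted mean number of sampled children per caregiver: m = 1 + 2 x (pairs both sampled)/520. For f = 10%, m = 1 + 24.3/520 = 1.047. An assumed ICC of 0.3 to 0.5 then gives 1.014 to 1.023. For f from 5% to 30% the range is about 1.01 to 1.07. For comparison, full carry-over at f = 10% raises the required sample size by a factor of 1/(1 − 0.0234)² = 1.049, and half carry-over by 1.024.

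**The case against.** The strongest objection is that this argues from silence in a condensed article. The full protocol may contain a rule on siblings, and the article speaks of dyads and pairs throughout. What stands is that such a rule cannot be excluded. But the article does describe the list, the draw, the ratio, the timing and who implements allocation, and followed as written these steps permit splitting.

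A reader might also infer more than the documents support:

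- **That the intervention goes to the caregiver and the home rather than the child.** It goes to both. The child attends sessions, receives the supplies and keeps a personal notebook. A control sibling has none of these, so full carry-over is a ceiling and not an expectation.
- **That many households will be split.** The documents give no figure for shared caregivers. They show that splitting can happen, not how often.
- **That correlated siblings invalidate the analysis.** Under individual 1:1 allocation, sampled pairs fall about equally into the same arm and opposite arms, so their correlation largely cancels in the variance of the difference. This point is minor.
- **That a false positive could result.** Spillover of the intervention to control children pulls the difference toward zero.
- **That this explains the shortage of power.** The shortfall comes from the sample-size inputs. Split households would only add to it slightly.

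It can also be said that same-arm allocation carries a design effect close in size to the dilution it removes. At half carry-over that is roughly true for sample size, but the design effect costs only precision, whereas split households bias the estimate.

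**Conclusion.** The concern holds as a small, avoidable weakness. The stated scheme allows children of one caregiver to be allocated to different arms, and any such split biases A versus B toward no difference.

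If 5% to 20% of listed children are in such pairs, about 1% to 5% of group B is exposed, and the 0.7 effect falls to no less than about 0.67. These figures assume a uniform sampling fraction, pairs only and full carry-over. The direction does not depend on the assumed share; the size does. It does not threaten the trial's conclusions on its own, and the reason to act is that prevention is cheap.

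**What to change.** Add one sentence to Randomization, using what is available before allocation. Consent is taken from caregivers before the baseline survey, caregivers answer a questionnaire in that survey, and allocation follows it. Either option works.

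1. **Allocate together.** Suggested wording: *Enrolled children who share a primary caregiver will be identified from the consent and baseline records before allocation and assigned to the same arm as one unit; the caregiver will be the cluster in the GEE.* The cost is a design effect of about 1.01 to 1.07 (assumed ICC 0.3 to 0.5, with 5% to 30% of listed children in pairs), and an imbalance of a few children between arms or within age cells.

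2. **Enrol at most one child per caregiver**, chosen at random, where the age cell has a spare child. After sampling, 1113 − 520 = 593 listed children remain, but that is a total over 13 age cells, and the article does not show that every cell has spares. The cost is less choice in filling age cells and slight under-representation of children from multi-child families. It also needs the list to be linked by caregiver before the draw, or a check at consent.

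The first option needs no replacements and fits the existing order of steps. Whichever is chosen, report how many enrolled children share a caregiver.
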